##### Statistical analysis

2.2.1.4.

Statistical analysis was performed using SPSS 27.0 software (IBM, SPSS Inc.).
1.To ensure consistency and reliability between multicenter research samples, it is first necessary to conduct a consistency analysis on the structural data, such as age and sex, of the included cases from each center and the International Hip Dysplasia Institute (IHDI) classification using the Cohen's kappa statistic. Simultaneously, the baseline characteristics (such as structural composition and pathological severity) of the included cohorts within each center must be consistent; imbalances in baseline characteristics were corrected by increasing the sample size.2.The included patients were divided into the non-limbus inversion group (A) and the limbus inversion group based on the presence of limbus inversion at closed reduction. The limbus inversion group was then further divided into the RLI group (B) and the resolved inverted limbus group (C) according to the state at final follow-up. A combination consisting of any two of the groups was organized into cohorts. Fisher's precision probability test was used to compare the difference between the sexes and affected sides, using analysis of variance to compare the different ages between the two groups. Differences in acetabular index was compared using Student's *t*-test. Chi-square test was used to compare IHDI classification, VAS and HHS, and Severin classification at the final follow-up, and analysis of variance was used to compare the MRI T1ρ mapping values and the difference in the initial magnitude of limbus inversion between groups B and C, as well as the difference between the initial magnitude of limbus inversion and that at the final follow-up in group B.3.ROC curve analysis was used to predict the cut-off value of the initial magnitude of limbus inversion in the case of persistent RLI as well as calculate its specificity, sensitivity, and statistical significance.4.Sample size calculation.In this study, ossification of the acetabular cartilage was the main observation; thus, improvement of the acetabular index was the most suitable observation indicator. The sample size calculation was based on the previously published acetabular index at the final follow-up in the group with RLI and the group without RLI after closed reduction (21.41°±3.61° and 18.88 ° ± 4.32° in the two groups, respectively) (15). The significance level *α*, the statistical power of the test, the ratio of the sample sizes in the two groups, and the percentage of patients lost to follow-up were set at 0.05, 0.9, 1:1, and 20%, respectively. The minimum sample size for each group was calculated to be 67 cases (134 cases in total). Therefore, at least 67 cases needed to be enrolled in the observation group and the control group, respectively.

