###### Exclusion criteria

2.2.2.1.2.

Exclusion criteria 1–3 are the same as previously listed exclusion criteria 1–3 (2.2.1.2);
4. Patients who refused inclusion in the study cohorts.For pediatric patients satisfying the inclusion/exclusion criteria, the basic measures of acetabular development including the acetabular index and central-edge angle were assessed using frontal pelvic radiographs; the magnitude of limbus inversion, cartilaginous acetabular index, and T1ρ mapping values were measured using MRI.

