##### Randomized blocks and interventions

2.2.2.2.

A randomized trial study design was the most appropriate approach to observe the efficacy of surgical intervention, with blinding techniques used during statistical analysis of the data. A double-blind study was not feasible because the surgeon was required to provide detailed information on the surgical regimen. The researchers in each center divided the RLI participants into two study cohorts based on the randomized block design, i.e., the surgery and non-surgery groups. After informed consent was obtained from the guardians of patients in the surgery group, clearance of the inverted limbus *via* arthrotomy was performed.

All surgeries were performed by pediatric hip joint surgeons with senior job titles *via* a bikini incision, and the inverted limbus tissue embedded between the acetabulum and femoral head was excised after arthrotomy without damaging the limbus-cartilage complex. After surgery, casts or braces were applied to immobilize single hips in abduction for 4 weeks and the patients gradually resumed walking after removal of external fixators. No special rehabilitation therapy was administered.

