### Research ethics approval

4.1.

The registration of clinical trials was completed prior to this study protocol (registration number: ChiCTR1900020996) and was approved by the Medical Ethics Committee of Shengjing Hospital of China Medical University.

This study will recruit pediatric patients who have undergone closed reduction. Pediatric patients who meet al.l inclusion criteria and do not meet any exclusion criteria will be considered for this study. Prior to enrollment in the study, researchers will explain the objectives and content of the study in detail to the guardians of study participants as well as discuss the surgical risks and benefits of RLI clearance after closed reduction; researchers will ensure that the guardians are fully informed of the study. The guardians of the study participants must provide written informed consent before any research activity may begin. Participation in this study is voluntary and may be withdrawn by the participants' guardians at any time.

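### Section 2.2.2.2 describes consent only for the surgery group and after the randomised division, against section 4.1; refusals could then fall in one arm only

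*Protocol article*

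**What the plan says.** Section 2.2.2.2 (Randomized blocks and interventions) gives a sequence. Researchers in each centre "divided the RLI participants into two study cohorts based on the randomized block design, i.e., the surgery and non-surgery groups". The next sentence begins "After informed consent was obtained from the guardians of patients in the surgery group" and goes on to the arthrotomy. The section mentions no other consent and none for the non-surgery group.

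Section 4.1 (Research ethics approval) sets a general rule: "The guardians of the study participants must provide written informed consent before any research activity may begin". It also describes what comes first: "Prior to enrollment in the study, researchers will explain the objectives and content of the study in detail to the guardians of study participants". That discussion is to "discuss the surgical risks and benefits of RLI clearance after closed reduction".

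Section 2.2.2.1.2 lists as exclusion criterion 4: "Patients who refused inclusion in the study cohorts". It does not say whether this applies before or after allocation, and it is not limited to one arm.

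Section 2.2.2.6 compares the surgical with the non-surgical cohort and does not say whether membership follows allocation or the treatment received.

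**The concern.** Randomisation is a research activity, so under section 4.1 the consent of every guardian should already be in hand when a child is allocated. Section 2.2.2.2 puts the only consent it mentions after the division, and only in the arm that means open hip surgery. A centre that works from section 2.2.2.2 would ask for consent with the arm known, and would ask in one arm only.

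Exclusion 4 makes this matter for the analysis. It speaks of the study cohorts, which is also the term section 2.2.2.2 uses for the two randomised groups. A centre could therefore take it to cover a guardian who declines after allocation to surgery. That child would leave the trial, or be counted as non-surgical, and nothing comparable would happen in the other arm. If refusal is related to prognosis, the arms are no longer comparable. This is the only randomised comparison of RLI clearance in the programme.

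**Working it through.** The point rests on reading the sections against each other. The arithmetic only shows what one-sided refusal could do.

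**1. The sections side by side**

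| Question | 2.2.2.2 | 4.1 | 2.2.2.1.2, exclusion 4 |
|---|---|---|---|
| Whose guardians? | Surgery group | All participants | Not limited to an arm |
| When? | After the division, before arthrotomy | Before any research activity | Not stated relative to allocation |
| Study or operative consent? | Not stated | Study consent, with surgical risks discussed | Refusal of inclusion |

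Sections 2.2.2.2 and 4.1 differ on who and when unless section 2.2.2.2 means a second, operative consent, which it does not say.

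The bias controls in section 2.2.2.5 do not close the gap. They blind the data measurers and check cohort composition as in part 2.2.1, where imbalance is corrected by enlarging the sample (section 2.2.1.4). A larger sample does not remove bias from one-sided refusal.

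**2. The only sample size in the article**

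It belongs to the retrospective part (section 2.2.1.4) and is borrowed here for scale. Inputs: acetabular index 21.41 (SD 3.61) against 18.88 (SD 4.32). Alpha, power, ratio and loss "were set at 0.05, 0.9, 1:1, and 20%, respectively".

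- Difference: 21.41 − 18.88 = 2.53 degrees.
- SD: √((3.61² + 4.32²)/2) = 3.98 degrees.
- n per group = 2 × (1.960 + 1.282)² × 3.98² / 2.53² = 52.03, rounded up to 53 (two-sided alpha assumed).
- With 20% loss: 53/0.80 = 66.25, rounded up to 67.

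The stated 67 per group reproduces.

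**3. Illustration: refusers dropped from the surgery arm**

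Assumptions, none of them in the documents: a share r of the surgery arm refuses; refusers differ from acceptors by g SD in mean acetabular index; 53 evaluable children per arm before refusal.

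- Bias = r × g × 3.98.
- Standard error = 3.98 × √(1/(53(1 − r)) + 1/53).
- Two-sided type I error = Φ(bias/SE − 1.96) + Φ(−bias/SE − 1.96).

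| r | g = 0.25: bias (type I error) | g = 0.5: bias (type I error) |
|---|---|---|
| 10% | 0.10° (0.052) | 0.20° (0.057) |
| 20% | 0.20° (0.057) | 0.40° (0.077) |
| 30% | 0.30° (0.064) | 0.60° (0.108) |

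**4. Illustration: refusers counted as non-surgical**

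Let Δ = g × 3.98, with equal arms that share a mean m. Acceptors then average m + rΔ and refusers m − (1 − r)Δ. Adding the refusers to the other arm moves its mean by −(1 − r)Δ × r/(1 + r). The spurious gap is rΔ + r(1 − r)Δ/(1 + r) = 2rΔ/(1 + r).

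- r = 10%, g = 0.25: 2 × 0.1 × 1.00/1.1 = 0.18°.
- r = 30%, g = 0.5: 2 × 0.3 × 1.99/1.3 = 0.92°.

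**5. Illustration: refusers analysed as allocated**

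There is no selection bias, only dilution. If refusers gain none of the effect, the contrast becomes (1 − r) × 2.53, that is 2.28, 2.02 or 1.77 degrees for r of 10%, 20% or 30%. Power with 53 per arm falls from 0.90 to 0.84, 0.74 or 0.63.

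**The case against.** The strongest reply is that section 4.1 already settles the matter. It covers all guardians, puts written consent before any research activity, and has the risks and benefits of clearance after closed reduction discussed before enrolment. That intervention belongs to part 2.2.2 only, so section 4.1 clearly reaches the randomised part. The sentence in section 2.2.2.2, placed just before the arthrotomy, can then be read as operative consent, which a surgical trial needs as well.

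Exclusion 4 is an eligibility rule. It is followed by baseline measurement of the eligible children and precedes allocation in document order. The wording in section 2.2.2.6 may simply restate the arm names; it is not an explicit as-treated rule. How refusers are analysed is often left to a fuller protocol or analysis plan, which is not shown.

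Most of this stands. A reader might infer that refusals do fall in one arm only and that the randomised comparison is broken. The documents do not support that: it is a possible consequence of one reading, not a stated design. Nor do they support a direction. It is tempting to suppose that guardians of children who look better refuse, so that the bias runs against surgery, but no section says so. The first primary outcome (section 2.3.1) is improvement in the acetabular index. If that is a change from baseline, a gap in level does not carry over degree for degree, and the sign could reverse.

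The reply does not remove the conflict in wording. Section 2.2.2.2 is the text a centre follows to allocate and treat, and it does not call its consent a second one. Even if operative consent was meant, a guardian can still decline surgery once the arm is known, and the article does not clearly keep that child in the allocated arm.

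**Conclusion.** The concern holds as an inconsistency with a possible consequence for bias. Sections 2.2.2.2 and 4.1 disagree, as written, on who gives consent and when, and must be reconciled. Read literally with exclusion 4, section 2.2.2.2 leaves room for refusers to be removed from, or moved out of, the surgery arm after allocation.

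The size cannot be derived from the documents, which give no refusal rate, no prognosis for refusers and no sample size for this part. The range of 0.1 to 0.6 degrees applies to acetabular index level with refusers dropped, on the assumptions in step 3 of the working. For scale only, that is 4% to 24% of 2.53 degrees; that figure contrasts RLI with no RLI after closed reduction and is not a planned effect of clearance.

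**What to change.** - **Section 2.2.2.2:** state that guardians of every eligible child give written consent to randomisation to either arm before allocation is revealed, in line with section 4.1. If a later operative consent is also taken, name it as separate.
- **Section 2.2.2.1.2:** state that exclusion 4 applies only before randomisation.
- **Section 2.2.2.6:** keep children whose guardians later decline surgery in their allocated arm for follow-up and for the primary analysis, and report their number.

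Section 2.2.2.2 is written in the past tense. If children have already been allocated, the report should state the order actually followed and the number of refusals in each arm.

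The cost is protocol and consent wording, with no added procedures. Recruitment may be slightly slower because some guardians will decline before randomisation. Refusers analysed as allocated dilute the effect somewhat, as step 5 of the working illustrates; consent to either arm taken beforehand may keep their number down.

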##### Prospective follow-up observation

2.2.2.3.

Prospective follow-up observation was performed for the two clinical cohorts, and frontal pelvic radiographs were reviewed every 6 months. Since development of the hip joint in children is a long-term process, the included pediatric patients needed to be followed until skeletal maturity. Data pooling was performed once every 2 years to compare the short-term and medium-term outcomes of hip joint morphological development between the two groups. MRI T1ρ mapping was used to quantitatively evaluate quality of the acetabular cartilage before and during postoperative follow-up. The evaluated aspects and parameters were the same as those specified in 2.2.1.

##### Adverse events observation

2.2.2.4.

Complications and adverse events in the surgical treatment group were recorded and classified according to the adverse event classification system described by Sink et al. (DOI:10.1007/s11999-012-2343-2). Grade I: no clinical relevance and no need to change routine postoperative care; Grade II: resolving spontaneously after simple outpatient management or outpatient observation; Grade III: requiring hospitalization or surgical treatment before resolution; Grade IV: chronic impairment of body functions. Grade III and IV events were included in the analysis of results.

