###### Inclusion criteria

2.2.2.1.1.

Inclusion criteria 1–5 are the same as the previously listed inclusion criteria 1–5 (2.2.1.1);

6. More than 1 year after closed reduction;7. Patients aged ≤5 years at follow-up;8. The magnitude of limbus inversion exceeded 32% of the horizontal depth of acetabular roof at follow-up (or the cut-off value obtained in Protocol 2.2.1);9. The acetabular index was ≤30° at follow-up (since an acetabular index>30° usually necessitates pelvic osteotomy).

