##### Statistical analysis

2.2.2.6.

Fisher's precision probability test was used to compare the difference between the sexes and affected sides, using analysis of variance to compare the different ages between the surgical and non-surgical cohorts. Differences in acetabular index was compared using Student's *t*-test. Chi-square test was used to compare IHDI classification, VAS and HHS, and Severin classification at the final follow-up, and analysis of variance was used to compare the MRI T1ρ mapping values and the incidence of Grade III and Grade IV adverse events.

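### Section 2.2.2.4 provides for grading adverse events in the surgery group, but 2.2.2.6 compares Grade III/IV incidence between surgery and non-surgery, so that comparison has no control numerator

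*Protocol article*

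**What the plan says.** Section 2.2.2.2 randomises children with residual limbus inversion (RLI) to a surgery or a non-surgery group. Section 2.2.2.3 follows both groups, with radiographs reviewed every 6 months, and evaluates in both the parameters listed in 2.2.1.

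Section 2.2.2.4, on adverse events, names one group: "Complications and adverse events in the surgical treatment group were recorded and classified according to the adverse event classification system". The two grades that matter are defined as "Grade III: requiring hospitalization or surgical treatment before resolution; Grade IV: chronic impairment of body functions". The section ends: "Grade III and IV events were included in the analysis of results".

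Section 2.2.2.6, the analysis section of the same study, states that "analysis of variance was used to compare the MRI T1ρ mapping values and the incidence of Grade III and Grade IV adverse events". The contrast is named earlier in that paragraph: "using analysis of variance to compare the different ages between the surgical and non-surgical cohorts".

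**The concern.** A between-arm comparison needs the same events to be sought and graded in both arms. The article describes that process for one arm and then plans the comparison.

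The control count cannot be assumed to be zero by construction. Grade III is a need for hospitalisation or surgery before resolution and Grade IV is chronic impairment, and neither definition is tied to limbus surgery. Children in the non-surgery arm keep the inverted limbus and are to be followed to skeletal maturity. In giving the reason for its entry limit on acetabular index, the article itself notes that later bony surgery is a usual consequence of a poor index: "since an acetabular index>30° usually necessitates pelvic osteotomy" (2.2.2.1.1, item 9).

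The study is meant to inform whether and when to operate on RLI (2.1). A safety comparison that counts serious events after surgery but not those without it would tilt that judgement against surgery, and would hide any later hospital care or operations that surgery prevents.

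**Working it through.** **Step 1. What is collected, by arm**

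| Item | Surgery arm | Non-surgery arm | Source |
|---|---|---|---|
| Number randomised (denominator) | yes | yes | 2.2.2.2 |
| Acetabular index, Severin classification, limbus inversion | yes | yes | 2.2.2.3 via 2.2.1.3; 2.3.1 |
| Avascular necrosis (AVN) | yes | yes | 2.2.2.3 via 2.2.1.3; 2.3.1 |
| VAS and HHS | yes | yes | 2.2.2.3 via 2.2.1.3; 2.3.2 |
| T1ρ values | yes | yes | 2.2.2.3; 2.3.2 |
| Graded adverse events, including hospitalisation and later surgery | yes | not provided for | 2.2.2.4 |
| Grade III/IV incidence compared | yes | yes | 2.2.2.6 |

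The last two rows do not fit together. The parameters of 2.2.1.3 do not include hospitalisation or later surgery, so 2.2.2.3 does not fill the gap.

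**Step 2. Direction of the bias**

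Let pS and pC be the true Grade III/IV rates in the surgery and non-surgery arms. The true difference is pS − pC. If unrecorded control events are counted as none, the reported difference is pS − 0. The error is (pS − 0) − (pS − pC) = pC, always against surgery. If the control data are treated as missing, no comparison can be made.

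**Step 3. Illustration of what that could do**

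The article gives no Grade III/IV rate and no sample size for this randomised study. The only stated size is 67 per group for the retrospective cohort (2.2.1.4), borrowed here as an assumption. It reproduces:

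- SD = √((3.61² + 4.32²)/2) = 3.981; difference = 21.41 − 18.88 = 2.53
- two-sided α 0.05, power 0.9: n = 2 × (3.981 × (1.960 + 1.2816)/2.53)² = 52.03, rounded up to 53
- 20% loss: 53/(1 − 0.20) = 66.25, rounded up to 67

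Now assume that the true rate is the same in both arms and that control events are counted as zero. Fisher's exact test is used for illustration (2.2.2.6 names analysis of variance). With 67 per arm, 5 events against 0 gives two-sided p = 2 × (67·66·65·64·63)/(134·133·132·131·130) = 0.058. Six against 0 multiplies this by 62/129, giving 0.028. So six or more surgical events would be declared a difference.

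| Assumed true rate, both arms | Expected control events lost (67 × rate) | P(false difference), control counted as 0 | P(false difference), both arms recorded |
|---|---|---|---|
| 2% | 1.3 | 0.002 | 0.001 |
| 5% | 3.4 | 0.118 | 0.013 |
| 10% | 6.7 | 0.672 | 0.024 |
| 15% | 10.0 | 0.949 | 0.029 |

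With 53 per arm, the third column becomes 0.001, 0.048, 0.439 and 0.826. The effect runs from negligible to near certain over this assumed range, so the illustration shows sensitivity and is not an estimate.

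**The case against.** The best defence is that this is a condensed article. Section 2.2.2.4 never says that only the surgical group is recorded, and the comparison in 2.2.2.6 could mean that both arms are recorded and the earlier sentence is loosely worded. That is possible. But the article is not silent on the matter: it has a section on adverse events that names one group, and a later section that needs two. The sections must be reconciled whichever was meant.

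A second objection is that the Grade I definition refers to postoperative care, so the scale may be intended for complications of surgery. Later surgery for dysplasia could then be an efficacy failure and not an adverse event. The article does not settle this. It is a reason to fix the definition in advance, and it does not remove the planned comparison.

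Three stronger readings are tempting, and the article does not support them.

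- A reader might infer that the study cannot weigh the harm of surgery against the harm of leaving RLI in place. Acetabular index, Severin classification, AVN, VAS and HHS are assessed in both arms, so dysplasia and AVN are covered. The gap is limited to graded events.
- A reader might infer that control harms are set to zero, or that the control arm has no denominator. No such rule is stated, and the denominator is the number randomised to non-surgery. What is missing is the graded count.
- A reader might derive a control event rate from the 11% and 38% residual dysplasia quoted in the Introduction. Those figures describe children after closed reduction generally. The randomised children are selected on RLI, age, acetabular index and absence of repeat surgery, and the article gives no proportion of dysplastic hips that go on to Grade III or IV events.

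**Conclusion.** The concern holds in a limited form. Sections 2.2.2.4 and 2.2.2.6 are inconsistent: events are graded in the surgical group, their incidence is compared between groups, and nothing in the article supplies the control count. Followed as written, the Grade III/IV comparison is one-sided. If uncollected control events were treated as none, it would be biased against surgery by the true control rate. That rate is not given, so the size of the bias is unknown. The illustrative probabilities rest on an assumed equal rate of 2% to 15%, a borrowed arm size and Fisher's test.

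The outcomes listed in 2.3 are not affected. Graded adverse events are not among them, and AVN, which is, is assessed in both arms. The point still deserves correction, because control events that are not recorded as they happen may be hard to recover reliably later.

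**What to change.** Amend 2.2.2.4 so that complications and adverse events in both randomised groups are recorded from randomisation, over the same period and by the same method, and graded on the same system. Recording should be as events occur and again at each scheduled follow-up. Tying it to the 6-monthly reviews alone could delay or miss events soon after surgery.

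State in advance whether later hip surgery counts as an adverse event, and apply that definition equally to both arms. Adapt the grade wording that refers to postoperative care so that it can be used for children who had no operation.

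In 2.2.2.6, report Grade III/IV incidence by randomised arm, with the risk difference and its 95% confidence interval.

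If control events will not be collected, report the surgical-arm events descriptively and delete the between-group comparison from 2.2.2.6.

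The cost is slightly more data entry for control patients, who are already under follow-up. The alternative costs nothing to run but gives up the comparison.
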